### **Study schedule**

March 2018 Start clinical part of the study, first patient included

September 2018 last patient included

January 2019 data analysed and manuscript draft written

March 2019 end of study

## **2. ETHICAL AND REGULATORY ASPECTS**

Before the study will be conducted, the protocol, the proposed patient information and consent form as well as other study-specific documents will be submitted to the Cantonal Ethics Committee Bern. Any amendment to the protocol must as well be approved by this institution.

The decision of the CEC concerning the conduct of the study will be made in writing to the Sponsor-Investigator before commencement of this study. The clinical study can only begin once approval from all required authorities has been received. Any additional requirements imposed by the authorities shall be implemented.

### **2.1 Ethical considerations**

#### **2.1.1 The potential gain of new knowledge obtained with this study, and its meaning for patients/society:**

With this study, we will be able to determine, if high flow nasal cannula therapy (HFNCT) provides a real benefit over medium flow or low nasal cannula therapy. This can be of use in emergency situations, where airway access is sometimes difficult to obtain as apnoeic oxygenation could prolong apnoea time until desaturation. Lower flow rates can be provided in almost all clinical settings, including preclinical situations and on medical wards through already available systems. For HFNCT, a specific device is necessary, the availability of which is very limited. If non-inferiority can be shown, it could result in a greater safety for all patients through widespread availability of oxygen therapy devices, at a reduced cost compared to HFNCT. Furthermore, there is no evidence available about the physiological

changes in anaesthetised patients undergoing HFNCT for a prolonged time, which now has been established as a standard procedure.

### **2.1.2 Assessment of the benefit/risk relationship for the patient.**

HFNCT and apnoeic oxygenation are concepts that have been provided with enough evidence to sustain their acceptance in clinical use. There have even been studies suggesting possibility of oxygenation, using very low flows of oxygen [7-9]. But both, high flow and low flow have never been directly compared for its influence on human physiology. However small the risk, desaturation in low-flow groups cannot be completely ruled out. But one of our endpoints is saturation of <92% after which the experiment will be discontinued. Saturation of 92% does not lead to any ischemic damage in healthy patients and all patients with known risks or vulnerability of ischemic events are excluded.

Furthermore,  $p_a\text{CO}_2$  will rise, this leads to a cerebral vasodilation. There is no data setting any threshold after which potential damage would occur, even though patients with  $p_a\text{CO}_2$  up to 250 mmHg have been shown to recover without any neurological impairment [4]. Our limit will be set at 80 mmHg, which therefore should not lead to any neurological damage whatsoever, especially since all patients with high vulnerability towards hypercapnia are excluded. Measuring near infrared spectroscopy (NIRS) will furthermore ensure, that cerebral perfusion will stay within normal limits.

$\text{CO}_2$  is known to have haemodynamic influence [10, 11], but our pilot data suggest that anaesthetic drugs like Propofol and Remifentanyl overrule this effect, as median blood pressure never exceeded 80mmHg.

Patients safety will not be compromised during the study time, as this procedure has shown to prevent desaturation up to 65 minutes [2, 12]. If unexpected difficult airway should occur in these patients, there is more time for securing the airway until desaturation will set in.

### **2.1.3 The methodology is ethically appropriate to gain new generalizable knowledge**

The patients are blinded to the randomisation. The responsible anaesthetist cannot influence the apnoea time (very low risk of creating bias). The four groups will be stratified according to BMI (16-25kg/m^2, 25-30 kg/m^2, 30-35 kg/m^2), smoker status (non-smoker, non-daily smoker, daily smoker) and age (18-40 years, > 40 years) in order to maintain statistical equality. The trial method is well suited to study the research question and the participating anaesthetists are comfortable and used to all four oxygenation possibilities. All patients that could be harmed through high levels of  $\text{CO}_2$  or desaturation are excluded from the study. The study group has a wide experience with HFNCT and has performed a similar study in children before (Riva et al, BJA, 2018, in press).

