| Measurements and procedures: | 
Eligible, consenting adults will be prepared for general anaesthesia in the usual way consisting of EKG, pulse-oximetry, Narcotrend™, a venous cannula and an arterial line for continuous blood pressure monitoring. They will receive additional non-invasive monitoring for this study, such as transcutaneous measurement of pCO2 and O2, NIRS, and thoracic electrical impedance tomography (EIT, PulmoVista® 500, Draeger, Luebeck, Germany)
 
Standard pre-oxygenation (until etO2 is > 90% or time > 3 minutes) will be done. Anaesthesia will be started (= "induction") using Propofol and Fentanyl i.v., using Narcotrend™ to measure depth of anaesthesia. All patients will receive a standard dose (Rocuronium, 0.9mg/kg) of neuromuscular blockage to facilitate airway management and total intravenous anaesthesia will be installed to maintain anaesthesia. Train of four measurement (TOF) will be confirmed full neuromuscular blockage with Rocuronium every 30 seconds. If necessary, additional dosage of neuromuscular blockage will be administered.
 
After administration of Rocuronium, possibility of mask ventilation will be confirmed and the sealed envelope with the randomization will then be opened. As a study intervention, the assigned method (HFNCT 70 l/min with either jaw thrust or laryngoscopy, or 10 l/min or 2l/min) will be installed and mask ventilation discontinued starting the apnoea period. Nasopharyngoscopy (EF-N slim, Acutronic, Hirzel, Switzerland) will confirm upper airway patency. Blood gas analysis will be conducted: baseline awake, start of apnoea, first minute after apnoea start, every 2 minutes thereafter with a maximum of 75ml in total. Other measurements (ECG, pulse-oximetry, blood pressure, NIRS, thoracic EIT, Narcotrend™, PtcO2, PtcCO2) will be measured continuously over the study period.
 
The study intervention will end when one of the following criteria (study end-points) is met: SpO2 <92%, PtcCO2 > 80 mmHg, pH < 7.10, potassium > 6.0 mmol/l, or time > 15 minutes.
 
When any of the end points is reached, patient-centred standard anaesthesia care will be continued, as planned for the case.
 
A post-operative interview will be conducted on the first post-operative day to evaluate injuries during airway management (e.g. bleeding, sore throat, hoarseness, lip injuries), pain, postoperative nausea and vomiting.
 |

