## **6.2 Methods of minimising bias**

### **6.2.1 Randomisation**

Patients will be assigned to their respective group using a computer-generated randomization list by [www.randomisation.com](http://www.randomisation.com). Randomisation will be stratified according to BMI in three groups: <25, 25-30 and >30 and smoker status (non-smoker, non-daily smokers and daily smokers < 40 years of age, daily smoker > 40 years of age).

Allocated group will be kept in sealed opaque envelopes opened after induction of anaesthesia when proper face-mask ventilation is confirmed. Patients excluded from the study before opening of the randomisation envelope (e.g. because of impossible mask ventilation) will be replaced as if not eligible for the study.

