### **6.2.2 Blinding procedures**

Patients are under general anaesthesia therefore blinded to the treatment group, but due to the different oxygen delivery systems study personnel in the operating theatre cannot be blinded.

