## **8.2 Administration of experimental and control interventions**

### **8.2.1 Experimental Intervention**

After apnoea sets in and mask ventilation is successfully established, randomization envelopes are opened and according to group allocation, one of the following oxygen delivery systems is applied.

The first group receives high-flow nasal cannula therapy with 70 l/min with 100% oxygen via OptiFlow™ by Fisher&Paykel™, Auckland, NewZealand, using jaw thrust.

The second group receives 10 l/min of 100% humidified oxygen using Carbamed digiflow, Aquapak Hudson RCI and nasal cannula

Third group receives low-flow 2l/min of 100% humidified oxygen using Carbamed digiflow, Aquapak Hudson RCI and nasal cannula.

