## 10. STATISTICAL METHODS

### 10.1 Hypothesis

Null hypothesis: The difference of the mean increase of  $p_{tc}CO_2$  between any of the three intervention groups and the control group is at least 0.3 mmHg/min, the control group being lower.

Primary hypothesis: the difference of the mean increase of  $p_{tc}CO_2$  between the groups is less than 0.3 mmHg/min (non-inferior margin), one-sided testing. This hypothesis was based on a small clinical pilot study that showed no differences regardless of flowrate or mouth opening (jaw-thrust vs. laryngoscopy).

Secondary outcome hypothesis: The number of patients not tolerating the apnoea time of 15 minutes is not significantly higher in any of the three intervention groups.

Secondary outcome hypothesis: no significant changes in vital parameters such as cerebral perfusion will be recorded.

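### Section 2.1.3 says the anaesthetist cannot influence apnoea time, but unblinded staff know the arm before mask ventilation stops, so starting CO2, and with it run length, is open to influence

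*Protocol*

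**What the plan says.** Section 2.1.3 of the protocol gives an unqualified assurance: "The responsible anaesthetist cannot influence the apnoea time (very low risk of creating bias".

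The order of events is given in three places.

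- Synopsis, measurements and procedures: after rocuronium, "possibility of mask ventilation will be confirmed and the sealed envelope with the randomization will then be opened". The assigned method "will be installed and mask ventilation discontinued starting the apnoea period".
- Section 6.2.1: envelopes are "opened after induction of anaesthesia when proper face-mask ventilation is confirmed".
- Section 8.2.1: "After apnoea sets in and mask ventilation is successfully established, randomization envelopes are opened".

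Section 6.2.2 accepts that "due to the different oxygen delivery systems study personnel in the operating theatre cannot be blinded", and section 6.3 calls the study open.

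Section 6.1 ends the run at the first of five criteria: SpO2 below 92%, transcutaneous CO2 above 80 mmHg, pH below 7.1, potassium above 6.0 mmol/l, or more than 15 minutes.

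Two secondary questions rest on run length. Section 4.3 names mean duration of apnoea, and section 10.1 states the hypothesis: "The number of patients not tolerating the apnoea time of 15 minutes is not significantly higher in any of the three intervention groups".

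**The concern.** By the synopsis, mask ventilation ends only once the assigned method is in place, which is after the envelope has been opened. Some ventilation is therefore given by people who know the arm. Nothing in the protocol fixes how long this lasts, and the arms use different equipment, so the interval could differ between them.

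Ventilation affects CO2 at the moment apnoea begins. A run that starts higher reaches 80 mmHg sooner at the same rate of rise. Mean duration and the count of patients not reaching 15 minutes combine all stopping criteria, so both could differ between arms because of ventilation given after allocation, with no difference in the effect of flow. The assurance in 2.1.3 rules this out by assertion.

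**Working it through.** **Inputs from the protocol.** Rate of rise 1.8 mmHg/min, SD 0.35, margin 0.3 mmHg/min, one-sided alpha 0.025, power 80%, 25 patients per group (10.2); CO2 limit 80 mmHg and 15-minute limit (6.1); transcutaneous delay of about 60 to 90 seconds (8.5.1). The only CO2 reference range is the normal arterial range of 35 to 46 mmHg (10.2). Starting CO2 and its spread are not given, so the starting values below are assumptions.

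**The plan's own figure.** n = 2 × (1.96 + 0.842)² × 0.35² / 0.3² = 21.4, rounded up to 22 per group. This reproduces section 10.2 and is not in dispute.

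**Start from which the average patient reaches the limit.** The rise over 15 minutes is 1.8 × 15 = 27 mmHg, so the average patient reaches 80 mmHg within the run only from a start above 80 − 27 = 53 mmHg. With a 90-second delay there are 13.5 minutes of visible rise, and the figure is 80 − 1.8 × 13.5 = 55.7 mmHg.

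**Chance of an early CO2 stop.** For start s and T minutes of rise, with a linear rise, a normally distributed rate and no other stopping criterion:

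P = 1 − Φ( ((80 − s)/T − 1.8) / 0.35 )

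| Start (mmHg) | T = 15 min | T = 13.5 min |
|---|---|---|
| 35 | 0.03% | <0.1% |
| 40 | 0.7% | <0.1% |
| 45 | 6.4% | 1.2% |
| 46 | 9.1% | 2.0% |
| 50 | 28% | 11% |

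Worked example, s = 46, T = 15: (34/15 − 1.8)/0.35 = 1.33, so P = 9.1%.

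**Sensitivity to the start.** A start 5 mmHg higher brings the 80 mmHg stop forward by 5/1.8 = 2.8 minutes. Per 25 patients (T = 15), expected early CO2 stops go from 0.2 to 1.6 between starts of 40 and 45 mmHg, and from 1.6 to 7.1 between 45 and 50 mmHg. A start difference of 0.3 × 15 = 4.5 mmHg affects CO2 at 15 minutes as much as the whole non-inferiority margin.

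**Start against the patient's own rate.** The rate alone gives an SD of 0.35 × 15 = 5.25 mmHg at 15 minutes. An assumed start SD of 3, 5 or 8 mmHg would supply 25%, 48% or 70% of the variance in CO2 at that time: for 5 mmHg, 25/(25 + 27.6) = 48%. The start is the larger source only if its SD exceeds 5.25 mmHg.

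**Primary outcome.** Section 8.5.1 divides the CO2 difference by time once the rise is linear. If CO2 = s + rate × time, s cancels from the difference.

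**The case against.** The sentence has a narrower reading. Once apnoea has begun, numerical criteria end it, and full neuromuscular block excludes breathing; the anaesthetist has no stated discretion over when to stop. Lack of blinding is declared openly in 6.2.2. This stands as an account of how a run ends, but 2.1.3 makes no such restriction and draws a conclusion about bias from it.

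A reader might go further and infer that starting CO2 largely decides whether a run is cut short. The documents do not support that. Across 35 to 46 mmHg an early CO2 stop is uncommon, the 28% needs a start outside that range, and the patient's own rate matters at least as much unless the start SD exceeds 5.25 mmHg.

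A reader might also infer that one and the same team ventilates and runs the study. The protocol does not say who ventilates, and section 6.1 keeps one anaesthesia staff member free of study duties.

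Ventilation before the envelope also sets the start, but with the arm unknown it cannot favour one. How far ventilation after the envelope shifts CO2 between arms cannot be estimated. Time to desaturation is already a separate secondary outcome (5.2), so the pooling of causes concerns only the outcomes in 4.3 and 10.1. A start-of-apnoea blood gas and continuous transcutaneous CO2 are planned, so an imbalance would be visible. These points limit the size of the concern; they do not restore the assurance.

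**Conclusion.** The assurance in 2.1.3 does not hold as written. Allocation is known to unblinded staff before mask ventilation stops, the interval to apnoea is not fixed, and CO2 at the start of apnoea can move the time to one of the stopping criteria. Mean apnoea duration and the number not completing 15 minutes are therefore open to influence after allocation.

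The size is unknown. The calculated range for early CO2 stops shows how sensitive these outcomes are to the start; it does not estimate bias between arms. It rests on the protocol's rate and SD, a linear rise and assumed starting values, and allowing for the transcutaneous delay lowers it. The primary non-inferiority comparison is spared under a linear rise. This is a moderate point about two secondary outcomes and one sentence of justification.

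**What to change.** 1. Correct the sentence in 2.1.3 and reconcile it with the synopsis, 6.2.1, 6.2.2 and 8.2.1. State one sequence and one time zero: 8.2.1 speaks of apnoea setting in before mask ventilation is established, while the synopsis starts the apnoea period when mask ventilation stops.
2. Open the envelope as late as possible: after mask ventilation is confirmed, the delivery systems are ready, and a pre-apnoea transcutaneous CO2 reading and blood gas have been taken. This keeps the purpose of 6.2.1, which is to replace patients who cannot be mask-ventilated before they are allocated.
3. Record the times of envelope opening and apnoea start on the CRF, and report starting CO2 by arm.
4. Adjust the duration and 15-minute analyses for the pre-allocation CO2. A value taken after allocation may itself carry the effect in question, so it should be described rather than relied on for adjustment.
5. Report runs shorter than 15 minutes by the criterion that ended them. The SAP, which is not shown, may already provide for this.

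No ventilation target or clinical start condition is proposed.

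The cost is wording, two time stamps, and having all delivery systems ready before allocation is known. If the pre-allocation blood gas is added rather than taken in place of the start-of-apnoea sample, the ten samples of about 7.5 ml in 8.5.3.2 become eleven, or 82.5 ml, above the stated 75 ml maximum; the protocol would need to say which is meant. The interval after allocation is shortened, not removed, so some room for influence remains and should be acknowledged.

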## **2.2 Study registration**

The study will be registered at [www.clinical-trials.org](http://www.clinical-trials.org), and at the database of the Inselspital Bern through the Clinical Trial Unit of the University of Bern, as well as the KOFAM of the BAG ([www.kofam.ch](http://www.kofam.ch)).

## **2.3 Categorisation of study**

Risk category A.

Rationale: No medication or device will be investigated. We compare a therapeutic strategy in three experimental and one standard therapy arm (= oxygen application is used every day

in anaesthesia in this setting).

## **2.5 Ethical Conduct of the Study**

The study will be carried out in accordance to the protocol and with principles enunciated in the current version of the Declaration of Helsinki, the guidelines of Good Clinical Practice (GCP) issued by ICH, in case of medical device: the European Directive on medical devices 93/42/EEC and the ISO Norm 14155 and ISO 14971, the Swiss Law and Swiss regulatory authority's requirements. The CEC and regulatory authorities will receive annual safety and interim reports and be informed about study stop/end in agreement with local requirements. A final report will be sent at least one year after study stop/end to CEC.

## **2.6 Declaration of interest**

There is no conflict of interest by any of the investigators.

## **2.7 Patient Information and Informed Consent**

The investigator will explain to each participant the nature of the study, its purpose, the procedures involved, the expected duration, the potential risks and benefits and any discomfort it may entail. Each participant will be informed that the participation in the study is voluntary and that he/she may withdraw from the study at any time and that withdrawal of consent will not affect his/her subsequent medical assistance and treatment.

The participants must be informed that the medical records may be examined by authorised individuals (e.g. CEC) other than their treating physician.

All participants of the study will be provided a study information sheet with a consent form describing the study and providing sufficient information for the participant to make an informed decision about their participation in the study at their anaesthesia visit before surgery (up to 3 weeks before and at least 24h before the intervention).

The study information sheet with the consent form will be submitted to the CEC to be reviewed and approved. The formal consent of the participant, using the approved consent form, must be obtained before the participant is submitted to any study procedure.

The study participant should read and consider the statement before signing and dating the informed consent form and should be given a copy of the signed document. The consent form must also be signed and dated by the investigator (or his designee) and it will be retained as part of the study records.

## **2.8 Participant privacy and confidentiality**

The investigators affirm and uphold the principle of the participant's right to privacy and that they shall comply with applicable privacy laws. Especially, anonymity of the participants shall be guaranteed when presenting the data at scientific meetings or publishing them in scientific journals.

Individual subject medical information obtained as a result of this study is considered confidential and disclosure to third parties is prohibited. Subject confidentiality will be further

ensured by utilising subject identification code numbers to correspond to treatment data in the computer files. The patient code is build using the patient identifier (from the Inselspital's SAP) multiplied by two. The patient identifier can only be obtained by Inselspital personnel.

The code will be stored in a lockable cupboard in the lockable office of the principal investigator where no one else has access.

For data verification purposes, authorised representatives of a competent authority (e.g. Swissmedic), or the cantonal ethics committee may require direct access to parts of the medical records relevant to the study, including participants' medical history.

## **2.9 Early termination of the study**

The Sponsor-Investigator may terminate the study prematurely according to certain circumstances, for example:

- ethical concerns
- insufficient participant recruitment
- when the safety of the participants is doubtful or at risk, respectively
- alterations in accepted clinical practice that make the continuation of a clinical trial unwise
- early evidence of harm of the experimental intervention

## **2.10 Protocol amendments**

Substantial amendments are only implemented after approval of the CEC. Under emergency circumstances, deviations from the protocol to protect the rights, safety and well-being of the study participants may proceed without prior approval of the sponsor and the CEC. Such deviations shall be documented and reported to the sponsor as soon as possible.

All Non-substantial amendments are communicated to the CEC within the Annual Safety Report (ASR).

# **3. BACKGROUND AND RATIONALE**

## **3.1 Background and Rationale**

Normally, after induction of general anaesthesia apnoea sets in. While waiting for optimal intubation conditions, manual mask ventilation ensures ventilation and oxygenation. An intubation is performed so the airway is secured, and ventilation can be operated mechanically by a respirator. If no measures to ensure ventilation after anaesthesia induction were taken, desaturation would set in within minutes.

Pre-oxygenation is part of preparation initiated before induction in order to fill up oxygen reserves in the patient's body (e.g. lungs and haemoglobin). Also, preparations to ensure swift tracheal intubation are made (e.g. neuromuscular blockage). Nevertheless, there is a phase, in which the patient is apnoeic, and a deoxygenation may occur. This phase, however short, cannot be avoided while placing the tube into the trachea.

If anaesthesia needs to be provided in emergency situations or in presence of a difficult airway, the rate of complication increases [1]. This is due to hindered or impossible preparation, difficult circumstances and prolonged intubation and therefore apnoea-time. In these circumstances methods to reduce desaturation incidents are desirable.

High-Flow nasal cannula therapy is the administration of heated, humidified oxygen via nasal

cannula at rates up to 100 l/min. This high-flow nasal cannula therapy was developed in the intensive care unit as an alternative to continuous pressure support (CPAP).

A new application for high-flow nasal cannula therapy in adults is the extension of apnoea time in patients with difficult airways who are undergoing general anaesthesia [2]. In this environment, a new term for this kind of oxygen therapy was created: THRIVE - transnasal humidified rapid-insufflation ventilatory exchange. It was described to have prolonged apnoea time up to 65 minutes [2, 3, 13].

THRIVE has shown to be a suitable method to prolong apnoea with stable O2 saturation [2, 3]. Despite promising pilot results with high-flow nasal cannula therapy, it is unknown whether this technique is superior to low-flow nasal cannula therapy. Especially the claimed ventilatory effect has not yet been provided with sufficient data. It is thought to happen through turbulences caused by the high flow, that continue down through the trachea into the alveoli. This turbulence is said to wash out CO2 because slower increase of CO2 has been described using THRIVE vs. normal apnoea. However, this data of normal apnoea was already acquired in 1959 by Frumin et al. on only 8 healthy patients [4]. Since then, many things, including technology and patient factors have changed and this data therefore has only limited application today.

Especially the CO2 clearance under different flow rates has yet to be thoroughly examined. This is important, as increased CO2 can cause a multitude of effects like acidosis and altered cerebral blood flow [4, 11, 14]. Our study will also examine the effect of increasing paCO2 on cerebral perfusion using NIRS.

Furthermore, we will compare HFNCT at 70 l/min performing jaw thrust, with a group of patients, who's mouths will be opened using continuous video laryngoscopy, which is a standard procedure today for laryngeal surgery. In our study, we will only apply the minimal strength required in order to keep the airway patent, which can be visually confirmed using the video-monitor. Whether laryngoscopy compared to jaw thrust makes any difference in oxygenation or CO2 increase has yet to be examined.

This study investigates under controlled circumstances the concept of THRIVE to prolong apnoea time without desaturation. With our findings, we hope to improve airway management safety. Furthermore, this study enables us to better understand physiology behind apnoeic oxygenation and the influence of different nasal flow rates. Our study's extensive setup also allows us to measure the effects of increased CO2 on cerebral blood flow and cardiac output.

